# Ablative radiation therapy to restrain everything safely treatable (ARREST): study protocol for a phase I trial treating polymetastatic cancer with stereotactic radiotherapy

**DOI:** 10.1186/s12885-021-08020-2

**Published:** 2021-04-14

**Keywords:** Stereotactic radiotherapy, Cancer, Metastatic disease, Clinical trial (phase I)

## Abstract

**Background:**

Patients with polymetastatic cancer are most often treated with systemic therapy to improve overall survival and/or delay progression, with palliative radiotherapy reserved for sites of symptomatic disease. Stereotactic ablative radiotherapy (SABR) has shown promise in the treatment of oligometastatic disease, but the utility of SABR in treating all sites of polymetastatic disease has yet to be evaluated. This study aims to evaluate the maximally tolerated dose (MTD) of SABR in patients with polymetastatic disease.

**Methods:**

Up to 48 patients with polymetastatic cancer (> 10 sites) will be enrolled on this phase I, modified 3 + 3 design trial. Eligible patients will have exhausted (or refused) standard systemic therapy options. SABR will be delivered as an escalating number of weekly fractions of 6 Gy, starting at 6 Gy × 2 weekly fractions (dose level 1). The highest dose level (dose level 4) will be 6 Gy × 5 weekly fractions. Feasibility and safety of SABR will be evaluated 6 weeks following treatment using a composite endpoint of successfully completing treatment as well as toxicity outcomes.

**Discussion:**

This study will be the first to explore delivering SABR in patients with polymetastatic disease. SABR will be planned using the guiding principles of: strict adherence to dose constraints, minimization of treatment burden, and minimization of toxicity. As this represents a novel use of radiotherapy, our phase I study will allow for careful selection of the MTD for exploration in future studies.

**Trial registration:**

This trial was prospectively registered in ClinicalTrials.gov as NCT04530513 on August 28, 2020.

**Supplementary Information:**

The online version contains supplementary material available at 10.1186/s12885-021-08020-2.

## Background

In patients who have metastatic cancer, cancer which has spread beyond the primary site to other distant sites in the body [1], the standard of care treatment is most often systemic therapy. Systemic therapy, which may include hormonal therapy, chemotherapy, targeted therapy and/or immunotherapy, has been the cornerstone of providing progression-free and overall survival advantages in patients who have metastatic cancer [2]. While systemic radiotherapy in the form of therapeutic radiopharmaceuticals are available or emerging as treatment for some polymetastatic cancers (i.e. neuroendocrine, thyroid, prostate cancer) [3], in most cases this treatment has been limited to the palliation of bone disease with bone seeking radiopharmaceuticals [4].

The traditional role of radiotherapy in patients who have metastatic cancer has been for palliation of symptomatic metastases where systemic therapy does not penetrate (i.e. brain metastases) [5], or targetable sites of disease causing symptoms such as pain, obstruction and/or bleeding [6–8]. The doses of radiation used for palliation are typically low, utilizing simple radiation planning techniques with the goal of obtaining symptom relief while minimizing treatment toxicity as well as financial toxicity and treatment burden.

Recent studies have examined a subset of patients with metastatic cancer who have a limited burden of metastatic disease, known as oligometastatic cancer. The oligometastatic state is best defined as a stage of disease where a cancer has spread beyond the primary tumour to a limited number of sites, but is not yet widely metastatic [9]. While definitions of oligometastatic cancer vary, most would consider the oligometastatic state to represent 1–3 or 1–5 metastatic lesions [10, 11].

Recent randomized trials have reported improvements in progression-free and overall survival with aggressive treatments directed at oligometastases [12–15], including stereotactic ablative radiotherapy (SABR). The application of ablative therapies for patients with 4–10 metastatic sites is being evaluated in the randomized phase III COMET-10 trial [16] where patients are randomized to ablative SABR to all sites of disease versus standard of care treatment.

In contrast to the oligometastatic state, the polymetastatic state exists beyond the oligometastatic state, where widespread dissemination of metastatic cancer has occurred (i.e. non-oligometastatic, > 10 sites of metastases) [17]. Even with recent improvements to systemic therapy options for patients who have polymetastatic cancer, it is expected that a patient’s cancer will eventually become resistant to systemic therapy, necessitating a switch to a different drug regimen. Eventually, these patients exhaust all available lines of systemic therapy and will succumb to their cancer.

As a single modality, radiotherapy is associated with higher response rates compared to most systemic therapies given with palliative intent [6]. However, it is only with recent advances in radiotherapy planning and delivery technology that SABR can be considered as potentially feasible to treat all sites of polymetastatic cancer. Given that SABR has shown promise in providing progression-free and overall survival advantages in the oligometastatic state, we postulate that the benefits of stereotactic radiotherapy may not be limited only to those with oligometastases.

The toxicity of SABR may depend primarily on the doses of radiotherapy delivered to organs at risk, rather than the number of metastatic sites treated [18]. For serial organs, such as the spinal cord, reducing the maximum point dose of radiation is expected to reduce the probability of toxicity. For parallel organs, such as the kidney and lung, reducing a critical volume of the organ receiving radiation from a specific dose of radiation is expected to reduce the probability of toxicity. For this trial, we will employ strict dose constraints for both serial and parallel structures which have been established as safe when utilizing SABR [19]. At the same time, cumulative low doses to larger volumes of tissue can be expected and may be a source of toxicity, although older literature employing hemi-body radiation suggests these doses may be tolerable [20].

Given the rationale behind expansion of the oligometastatic paradigm (i.e. with the COMET-10 trial), we believe it is reasonable to postulate that the benefits of stereotactic radiotherapy may be independent of lesion number provided the treatment can be performed without excess radiation related toxicity. In this modified phase I dose escalation trial, we will test the hypothesis that SABR can be safely delivered to all sites of polymetastatic (> 10 lesions) cancer in patients for whom standard of care systemic therapies have been exhausted (or if additional systemic therapy is refused) to determine the maximally tolerated dose (MTD).

## Methods/design

### Objective

The objective of this trial is to assess the safety and feasibility of delivering SABR to patients with polymetastatic cancer (greater than 10 sites of disease) by establishing the MTD of SABR when given at 6 Gy per fraction.

### Study design

This is a modified 3 + 3 design Phase I dose escalation trial. Participants will be from a single tertiary academic radiotherapy department in Canada. Three patients will initially be treated at dose level 1, 12 Gy in 2 fractions over 2 weeks, with evaluation of toxicity occurring 6 weeks after completion of treatment. If the composite co-primary endpoints are met, subsequent dose escalations will be accomplished by increasing the number of 6 Gy weekly fractions up to a maximum dose level of 30 Gy in 5 fractions over 5 weeks (Fig. 1). Given the potentially wide variety of anatomic scenarios for polymetastatic disease and the potential planning challenges beyond clinical tolerability, dosimetric planning feasibility will be evaluated with a planning success rate of greater than 33% deemed as acceptable for each dose level. Thus, a total of 12 patients per dose level could potentially be accrued to fully determine the clinical and technical feasibility.

**Fig. 1 Fig1:**
[figure not shown]
Schema of the ARREST clinical trial. The initial dose level will be 6 Gy in 2 weekly fractions, with subsequent dose escalations to be achieved by increasing the number of weekly fractions for each dose level until the maximum dose level of 6Gy in 5 weekly fractions is achieved. DLT will be assessed 6 weeks after completion of radiotherapy

#### Endpoints

##### Co-primary safety endpoint

For a given patient, safety of treatment at a given dose level will be determined by meeting all of the following criteria:
The patient successfully receives all treatment at the assigned dose levelNo Grade 5 toxicity (patient death) attributable to treatment occurs.No Grade 4 toxicity (CTCAE v4.0) at the 6-week assessment among hematologic, cardiac, hepatobiliary or respiratory domains.No more than three instances of Grade 3–4 toxicities among other domains.

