##### Special considerations during radiotherapy delivery

Given the large volume irradiated, pre-treatment with anti-emetics is mandatory for all patients on this study. The preferred treatment regimen will be ondansetron 8 mg 1–2 h prior to each radiotherapy fraction.

Patients are required to have bloodwork demonstrating adequate bone marrow function prior to delivery of the second fraction of radiotherapy, and every fraction thereafter. It is suggested this bloodwork be taken either after the last treatment of the previous level or on the first day of the next dose level, and reviewed by the treating oncologist prior to delivery of the next dose level of radiotherapy treatments. One repeat draw of bloodwork is permitted if the bloodwork values are just below the thresholds listed below. Criteria for stopping radiotherapy due to concerns of inadequate bone marrow function will be: CTCAE grade 3 anemia (hemoglobin less than 80 or symptomatic requiring a transfusion); CTCAE grade 3 thrombocytopenia (platelets less than 50), CTCAE grade 3 neutropenia (absolute neutrophil count less than 1).

Patients are not allowed to receive cytotoxic, immunotherapeutic or molecularly targeted agents within a time period commencing 2 weeks prior to initiation of radiotherapy until 6 weeks after completion of therapy. Patients on conventional hormone therapy (i.e. anti-estrogen or anti-testosterone therapy) may continue these medications.

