##### Follow-up evaluation

Patient will be seen 6 weeks post treatment to evaluate short-term treatment toxicity. If patients cannot travel for this visit (or refuse to travel), an attempt will be made to contact the patient by phone to complete follow-up information. It must be documented if follow-up information is being gathered by telephone. The FACT-G and EQ-5D-5L quality of life questionnaire will be completed at that visit. Further follow-up will be according to physician discretion; a recommended frequency would be every 3 months at minimum. Follow-up investigations will be at the physician’s discretion. While routine reimaging is not required, a follow-up CT of the head, chest, abdomen, and pelvis at 3 months post-treatment or at the time of symptomatic progression is suggested.

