##### Dose escalation criteria

For a given dose level, toxicity as DLT will be assessed after three patients have been treated at a given dose level at the 6-week assessment post treatment. If all three patients meet the co-primary safety endpoint, escalation to the next dose level will occur. If two or three patients fail the co-primary safety endpoint, the MTD will be determined as the dose level preceding the failed dose level. If one patient fails the co-primary safety endpoint, an additional three patients will be accrued at that dose level. If one or more of these additional three patients fail the co-primary safety endpoint, the MTD will be determined as the dose level preceding the failed dose level. If all three additional patients meet the co-primary safety endpoint (i.e. a cumulative five of six patients pass the co-primary safety endpoint), dose escalation to the next level will occur. All patients at a given dose level must be assessed for 6-week toxicity before escalation to the next dose level can occur.

Treatment planning futility will be considered if less than 33% of the patients (to a maximum of 9 patients) at a specific dose level can successfully have a treatment plan generated for that dose level meeting organ at risk constraints. If treatment planning futility is encountered, the MTD will be considered as the dose level preceding the failed dose level.

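### The Grade 4 criterion for four organ domains is tied to the 6-week assessment with no look-back window, so a resolved event can go uncounted and favour escalation

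*Protocol article*

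**What the plan says.** The co-primary safety endpoint in the protocol article has four parts. The patient must receive all treatment at the assigned level and must not die of treatment. The third part is "No Grade 4 toxicity (CTCAE v4.0) at the 6-week assessment among hematologic, cardiac, hepatobiliary or respiratory domains". The fourth is "No more than three instances of Grade 3–4 toxicities among other domains". Only the third is tied to a point in time.

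The other places that deal with timing repeat the same point and give no period:

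- Fig. 1 caption: "DLT will be assessed 6 weeks after completion of radiotherapy".
- Dose escalation criteria: "toxicity as DLT will be assessed after three patients have been treated at a given dose level at the 6-week assessment post treatment".
- Follow-up evaluation: "Patient will be seen 6 weeks post treatment to evaluate short-term treatment toxicity". If the patient cannot or will not travel, "an attempt will be made to contact the patient by phone to complete follow-up information".

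On laboratory tests, the section on special considerations during radiotherapy delivery says: "Patients are required to have bloodwork demonstrating adequate bone marrow function prior to delivery of the second fraction of radiotherapy, and every fraction thereafter". The article names no later blood test.

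**The concern.** Dose-limiting toxicity is usually counted as the worst grade over a stated period. Here the criterion for the four named domains can be read as the grade present on one day. The effect is odd: a Grade 4 event in another domain counts towards the fourth criterion whenever it happens, while one in a named domain may not count at all if it has resolved by week 6.

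This criterion feeds every escalation decision and the MTD. With cohorts of three, one patient classified differently can turn an escalation into an expansion, or an expansion into a stop. An uncounted failure can only push towards escalation.

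**Working it through.** **1. The plan's own figure.** Four escalation levels × 12 patients = 48, the stated maximum. It reproduces and is not affected. The article states no target failure rate and no operating characteristics, so the rates below are assumptions.

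**2. One hypothetical patient against the four criteria.** Suppose a Grade 4 event in a named domain starts after the last fraction and has resolved by week 6.

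| Criterion | Result, read literally |
|---|---|
| All treatment received | Met: the last fraction was given |
| No treatment-related death | Met |
| No Grade 4 in the four domains, at week 6 | Met: not present at that time |
| Limit on Grade 3–4 in other domains | Does not apply to this event |

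The patient passes.

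**3. The escalation rule.** Under the dose escalation criteria, a level passes with no failures in three patients, or with one failure in the first three and none in the next three. With counted failure rate q:

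P(pass) = (1−q)³ + 3q(1−q)² × (1−q)³

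If the true rate is p and a share m of failures goes uncounted, q = p(1−m).

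**4. True rate p = 1/3 (assumed).**

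| Share uncounted, m | Counted rate, q | P(pass) |
|---|---|---|
| 0 | 1/3 | 0.296 + 0.444 × 0.296 = 0.43 |
| 1/3 | 2/9 | 0.471 + 0.403 × 0.471 = 0.66 |
| 2/3 | 1/9 | 0.702 + 0.263 × 0.702 = 0.89 |

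The last row is close to a worst case. It arises if every failure is a Grade 4 event in the four domains that starts after the last fraction, with onset uniform over the six weeks and a duration of two weeks. Then 2/6 are present at the visit and 4/6 are not. The middle row arises if only half of failures are of that kind and two thirds of those are missed: 0.5 × 2/3 = 1/3.

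**5. Other assumed rates.**

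| True rate | m = 0 | m = 25% | m = 50% |
|---|---|---|---|
| 30% | 0.494 | 0.654 | 0.814 |
| 40% | 0.309 | 0.494 | 0.709 |
| 50% | 0.172 | 0.351 | 0.600 |

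The effect can also be small. At a true rate of 40%, if a quarter of failures fall under the anchored criterion and a quarter of those are missed, m = 0.25 × 0.25 = 0.0625, q = 0.375 and P(pass) = 0.351, against 0.309 with full counting.

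**The case against.** The strongest reply is that the phrase names the visit at which toxicity since treatment is reviewed. The follow-up section supports this, since it describes the visit's purpose as evaluating short-term toxicity. That reading is fair, and it means events can be missed, not that they are. It does not remove the problem: two assessors could classify the same patient differently, and the text gives neither of them a window.

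The gap is also narrow. Three of the four criteria have no time anchor. A cytopenia that meets the stopping criteria before a later fraction ends radiotherapy, so the patient fails on completion. The DSMC reviews the chart of any Grade 4–5 case. All of this stands, although the DSMC meets annually and its review is not part of the escalation rule.

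A reader might go further and infer that no blood test is required at week 6, so that laboratory grades cannot be determined. The article does not support that. The sentence "Follow-up investigations will be at the physician’s discretion" comes after the one on further follow-up and most naturally describes the period after the 6-week visit. The bloodwork before each fraction is a check on whether to proceed, not the toxicity schedule. Phone contact is a fallback and does not rule out local bloods. A week-6 laboratory schedule may well stand in the full protocol, which is not shown.

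**Conclusion.** The point holds as an ambiguity in the endpoint that should be settled before its results are used to escalate. Read literally, one of the four criteria lets a resolved Grade 4 event in the four named domains go uncounted, and any such miss favours escalation.

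Its size cannot be fixed from the article. At an assumed true failure rate of 33%, the chance that a level passes rises from 0.43 to 0.66 or 0.89 as one third or two thirds of failures go uncounted. The 0.89 should not be read as the expected effect. It needs every failure to be a short-lived Grade 4 event in these domains with onset after treatment, which nothing in the article establishes. Nor does the article show that dose-limiting events in general are missed.

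**What to change.** In the co-primary safety endpoint, replace the reference to the 6-week assessment in the third criterion with the worst treatment-attributable grade at any time from the first fraction through that assessment. Align the Fig. 1 caption, the follow-up section and the dose escalation criteria with this window. State how interim events and laboratory-graded toxicity are obtained when the 6-week contact is by phone, for example from local laboratory results.

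The attribution qualifier is new for this criterion. It matches the criterion on deaths and the DSMC's review of relatedness. Without it, a longer window would count events caused by advanced disease.

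Two changes should be avoided. The fourth criterion has no time limit, and applying the window to it would narrow it. Patients with phone contact only should not be replaced: they may be the sickest, and dropping them could itself favour escalation.

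No grade threshold, dose or maximum sample size changes. The cost is a sentence in the endpoint, matching edits elsewhere, somewhat more failures counted and, at most, one routine blood draw per patient.

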##### Data and safety monitoring committee

The DSMC will meet annually after study initiation to review toxicity. The DSMC will review the chart of any case of grade 4–5 toxicity to determine if such toxicity is related to treatment. If the DSMC deems that toxicity rates are excessive (> 40% grade 4 toxicity, or any grade 5 toxicity), then the DSMC can, at its discretion, recommend cessation of the trial, dose adjustment, or exclusion of certain treatment sites and/or delivery techniques that are deemed as high-risk for complications.

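### A cohort in which all three patients have Grade 4 toxicity outside the four named domains records no safety failures and escalates, although that rate exceeds the level the DSMC section calls excessive

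*Protocol article*

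**What the plan says.** Four parts of the protocol article bear on this point.

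- **Co-primary safety endpoint.** A patient passes only if four criteria are all met. The first is receipt of all assigned treatment. The second is no treatment-attributable death. The third is "No Grade 4 toxicity (CTCAE v4.0) at the 6-week assessment among hematologic, cardiac, hepatobiliary or respiratory domains". The fourth is "No more than three instances of Grade 3–4 toxicities among other domains".
- **Dose escalation criteria.** "If all three patients meet the co-primary safety endpoint, escalation to the next dose level will occur". After one failure in three, three more patients are treated, and the level is passed if "a cumulative five of six patients pass the co-primary safety endpoint". All 6-week assessments at a level must be in before escalation. The section does not mention the DSMC.
- **Data and safety monitoring committee.** "The DSMC will meet annually after study initiation to review toxicity". The committee reviews the chart of every Grade 4–5 case for relatedness, with no timing given. Toxicity is called excessive at more than "40% grade 4 toxicity, or any grade 5 toxicity". Neither domains nor a denominator are named. If the committee finds toxicity excessive, it "can, at its discretion, recommend cessation of the trial, dose adjustment" or exclude certain sites or techniques.
- **Special considerations during radiotherapy delivery.** Blood counts are checked before the second and every later fraction, and Grade 3 anemia, thrombocytopenia or neutropenia is a criterion for stopping radiotherapy.

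**The concern.** The MTD is the trial's objective, and the safety endpoint is the only toxicity input to the rule that sets it. Outside the four named domains that endpoint counts Grade 3 and Grade 4 alike and tolerates three of either. The DSMC section judges the same patients by the share with Grade 4 toxicity. The two yardsticks can therefore disagree about one cohort, and the protocol does not say which prevails or in what order they apply.

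There is also a gap in the grades. The third criterion names only Grade 4, and the fourth covers only the remaining domains. A Grade 3 cardiac, hepatobiliary or respiratory event falls under neither. Four Grade 3 events in the remaining domains fail a patient, while any number in these three domains does not, provided treatment is completed. The article does not say whether this is intended.

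At stake is that the next cohort is treated at a higher dose, or a level is reported as tolerated, before anyone has considered a Grade 4 rate that the protocol itself calls excessive.

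**Working it through.** **The plan's own escalation outcomes.** With 0 failures in the first three, the level is passed (0/3). With 1 failure and then 0 in the next three, it is passed (1/6, so five of six pass). Every other path stops. This agrees with the text. The maximum sample size, 4 levels × 12 = 48, is also reproduced and is not affected.

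**Per-patient result under the four criteria**

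| Patient | Result |
|---|---|
| Treatment complete, three Grade 4 events in other domains | Pass |
| Treatment complete, four Grade 4 events in other domains | Fail (criterion 4) |
| One Grade 4 event in a named domain at 6 weeks | Fail (criterion 3) |
| Treatment complete, any number of Grade 3 cardiac, hepatobiliary or respiratory events | Pass |
| Grade 3 blood count before fraction 2 or later that stops radiotherapy | Fail (criterion 1) |
| Grade 3 blood count arising after the last pre-fraction check | Pass |

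**Per-cohort result.** Three patients complete treatment, each with one to three Grade 4 events in other domains and no other failing event. Failures: 0/3, so the rule escalates. Grade 4 events: up to 3 × 3 = 9. Patients with Grade 4: 3/3 = 100%, against the 40% level. Two affected patients are enough to exceed it, with one event each: 2/3 = 67%. One is not: 1/3 = 33%.

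**Effect of the denominator.** The rate is taken as the share of patients with at least one Grade 4 event judged related. For a single affected cohort at level k, assuming three treated patients per level and no Grade 4 earlier, the pooled share is 3/(3k):

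| Level | Per cohort | Pooled | Pooled above 40%? |
|---|---|---|---|
| 1 | 100% | 3/3 = 100% | Yes |
| 2 | 100% | 3/6 = 50% | Yes |
| 3 | 100% | 3/9 = 33% | No |
| 4 | 100% | 3/12 = 25% | No |

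If two consecutive cohorts are affected, the pooled share is 6/9 = 67% after levels 2 and 3, or 6/12 = 50% after levels 3 and 4. Patients who fail planning and are treated at a lower level are also followed for toxicity; including them without Grade 4 events would lower the pooled shares further.

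**How likely.** The article gives no Grade 4 rate, so q is an assumption: each patient independently has one to three Grade 4 events in other domains with probability q, and nothing else fails anyone. Every cohort of three then escalates. The chance that it does so with more than 40% affected is P(at least 2 of 3) = 3q²(1 − q) + q³:

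| q | 20% | 30% | 40% | 50% | 60% |
|---|---|---|---|---|---|
| Escalates with more than 40% affected | 0.10 | 0.22 | 0.35 | 0.50 | 0.65 |

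**Timing.** Treatment plus the 6-week assessment takes 2 + 6 = 8, 3 + 6 = 9, 4 + 6 = 10 and 5 + 6 = 11 weeks at levels 1 to 4, in total 38 weeks. This is the fastest case: each cohort starts together and the next follows at once. All four levels could then fall between two annual meetings.

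**The case against.** The strongest defence is that the two sections do different jobs. The safety endpoint is a per-patient pass or fail. The DSMC is a wider backstop, useful because it can catch what the per-patient rule lets through, and it reviews every Grade 4–5 chart. The Discussion expects heavily pretreated patients, so some tolerance of severe events may be deliberate, and which events are dose-limiting is a clinical judgement. All of this is fair. A difference between the sections is not in itself an error. But a backstop works only if it acts before the step it guards, and here the chart review has no stated timing while escalation follows once the 6-week assessments are in.

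Three stronger readings are tempting, and the documents do not support them.

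- A reader might infer that Grade 3 events in all four named domains are never counted. That is wrong for the hematologic domain: a Grade 3 count that stops radiotherapy fails the patient through incomplete treatment. An event in any domain that prevents completion does the same.
- A reader might infer that the endpoint is blind to severe events in those organs. It is not: one Grade 4 event there at 6 weeks, or an attributable death, fails the patient.
- A reader might infer that the DSMC rule would stop such a level. The committee may only recommend, at its discretion, and on a pooled denominator one affected cohort at level 3 or 4 stays below 40%.

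The cohort with nine Grade 4 events is an extreme. The conflict does not depend on it, since two patients with one event each suffice on a per-cohort count.

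**Conclusion.** The point holds in limited form. A cohort whose three patients all complete treatment with Grade 4 toxicity outside the four named domains has 0/3 failures and escalates. At level 4, where there is no higher level, it counts as tolerated. Its Grade 4 rate of 100% exceeds the protocol's own 40% mark per cohort, and at level 1 also when pooled over the three patients treated. From level 2 on, the pooled answer depends on a denominator the article does not give.

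This assumes that the events are judged related, that nothing else fails a patient, and, for the pooled figures, three patients per level with no earlier Grade 4. Separately, Grade 3 cardiac, hepatobiliary and respiratory events enter neither toxicity count, nor does hematologic Grade 3 arising after the last pre-fraction check. Nothing in the escalation section makes the next level, or the MTD, wait for the committee.

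**What to change.** 1. Reconcile the Co-primary safety endpoint, the Dose escalation criteria and the DSMC section on Grade 4 events outside the four named domains. State the intent for Grade 3 cardiac, hepatobiliary and respiratory events. Which events are dose-limiting is for the investigators to decide. Merely extending the tally of three to all domains would not remove the conflict, because three Grade 4 events would still pass.
2. State the denominator of the 40% figure: patients at the current level or all treated patients, and whether those treated at a lower level after a planning failure are included.
3. In the Dose escalation criteria, make escalation, or declaration of the MTD, conditional on completion of the DSMC's existing Grade 4–5 chart review whenever a level exceeds the DSMC threshold.

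The cost is wording and a possible short wait at the affected levels. The section already waits for all 6-week assessments, so the review can be placed there. No sample size figure changes.
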